### 2.5. Clinical and Cognitive Measures

All data will be securely stored in an electronic data capture system called Research Electronic Data Capture (REDCap) (https://redcapbrasil.com.br/).

The validated Portuguese versions of the clinical and sociodemographic assessment scales will be applied during screening, at baseline, in the active phase (after the 6th session) and during follow-up (one week, three months, and six months after the last session), as shown in Table 1. The co-primary outcome scales are the HAMD17 [17] and the Autobiographical Memory Task (AMT) [32]. Remission will be defined as a final HAMD17 score less than or equal to 7 points, and a 50% reduction in score compared to baseline assessment will be considered a response. 

Experienced neuropsychologists will perform a cognitive assessment, which will last approximately 120 min, at baseline and at follow-up (one week and six months after the last session), as shown in Table 2.

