### 2.9. Statistical Analysis

Statistical analyses will be performed in R. The results will be considered statistically significant only if both conditions are met, that is, non-inferiority for the depression outcome, under unilateral *p* < 0.025, and superiority for the cognitive outcome, under *p* bilateral < 0.05. The following groups will be considered: experimental (E), corresponding to MST, and control/comparison (C), corresponding to ECT.

For the co-primary outcome depression (HAMD17), non-inferiority will be assessed by calculating the difference between the means of groups E and C and its 95% confidence interval at the end of the 12th session, which will then be compared to the NI margin (Ha: C-E < NI). Analyses will be performed on modified intent-to-treat (ITT) samples (at least 8 sessions of ECT/MST) and per-protocol (PP).

For the co-primary cognitive outcome (AMT [32]), we will perform linear hierarchical model analyses using a first-order regressive covariance structure, which includes all observed variables without the need to enter data for missing values. The dependent variable is the AMT score [32], the independent variables are time (all observations through week 6) and group. We will test the statistical significance of this interaction according to our superiority hypotheses controlled for age, years of schooling, and treatment-resistant depression (Ha: C-E < 0). Analyses will be performed on the ITT and PP sample.

The same linear hierarchical models will be used for all continuous secondary outcomes. We will assess response and sustained remission, that is, a clinical improvement of symptoms ≥50% (response) and a HAMD17 score ≤7 (remission) at a given point in the study, which will be maintained until the outcome. The trajectories of response and sustained remission between groups will be compared using Kaplan–Meier survival analysis. Response and remission will be compared considering non-inferiority margins of 20% and 15%, respectively. The choice of a 15% non-inferiority margin was based on the consideration that achieving a remission rate of 35% holds clinical relevance in this population with difficult-to-treat depression. Furthermore, this remission rate surpasses those achieved by more conventional and less invasive treatment options for TDR, such as repetitive TMS (rTMS) with an approximate remission rate of 20% [66] and antidepressants with a remission rate of 14% [1].

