### 2.10. Sample Size Calculation

The software programs G * Power 3 [67] from Universität Düsseldorf, Germany, and Stata (Statacorp, College Station, TX, USA) were used to conduct calculations. The sample size was determined using parameters of α = 0.025 (one-tailed), β = 0.2, and a standard deviation of 9.5. The margin of non-inferiority (NI) was determined based on a combination of statistical reasoning and clinical judgment [68]. The lower bound of the confidence interval from a meta-analysis comparing ECT vs. sham was used to establish the NI [69]. Using a meta-analysis by the UK ECT Review Group [16], the difference in HAMD17 scores between ECT and placebo was 9.7 points (95% CI 5.7 to 13.5), with an NI value of 5.7. Despite the large margin, this NI value was deemed acceptable due to the cognitive effects of bitemporal ECT (the control comparison). Thus, MST would be a reasonable non-inferior intervention, as cognitive superiority would also need to be demonstrated. The sample size required was 88 patients, with an additional enrollment of 10% (total of 100 patients, 50 per arm) to account for attrition. For the superiority analysis, we used data from an unpublished clinical trial of 75 patients that compared the efficacy and cognitive outcomes of MST vs. ECT (personal communication from [name]). The effect size of AMT [32] after 12 treatment sessions was approximately 1.31, requiring a sample size of 26 patients to demonstrate a difference. Thus, the larger sample size from the clinical outcome study was used for the NI calculation.

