## 3. Discussion

ECT is an effective alternative for treating TRD, albeit with limitations attributed to cognitive side effects [18]. Recent advancements in therapeutic modalities have introduced alternative agents and neuromodulation techniques, such as MST. By utilizing a magnetic field, MST offers a potential solution to the cognitive side effects associated with ECT by inducing seizures without directly stimulating deeper brain structures [70]. The objective of this study is to present a double-blinded, randomized, non-inferiority trial that compares the efficacy, tolerability, cognitive adverse effects, and neurophysiological biomarkers of MST to BT ECT in patients diagnosed with treatment-resistant unipolar or bipolar depression.

The primary outcome measure will be the reduction in depressive symptoms, assessed using the HAMD scale. Secondary outcome measures will include response rates, remission rates, and cognitive functioning assessed through comprehensive neuropsychological testing. Simultaneously, the evaluated biomarkers include multimodal MRI and serum BDNF levels. Evaluation of outcomes will be conducted at baseline, during the active treatment phase, and throughout a 6-month follow-up period.

Building upon previous research, the proposed protocol explores the potential of utilizing MST as an alternative form of convulsive therapy for TDR. This represents a significant advancement in the field.

The initial experiments with MST demonstrated its feasibility, tolerability, and effectiveness in both non-human primates and humans [71,72]. Shortly after, a double-blind randomized trial comparing the side effects of ECT and MST in patients diagnosed with major depression reported fewer subjective side effects and lower rates of disorientation, inattention, retrograde amnesia, and impairment of verbal fluency in the immediate post-ictal period for patients undergoing MST [70]. Since then, several studies have investigated the efficacy of MST for the treatment of depression, particularly when compared to ECT [73,74,75,76]. In general, recent studies provide support for the hypothesis that MST, when compared to ECT, exhibits non-inferiority in terms of antidepressant effects [77,78,79] and demonstrates a more favorable cognitive profile [73,74,75,77,80,81]. 

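### Section 2.9 writes the HAMD17 non-inferiority alternative as C-E < NI without saying whether the means are scores or reductions; on the HAMD17 score itself the inequality is reversed

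*Protocol article*

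**What the plan says.** Section 2.9 labels the groups "experimental (E), corresponding to MST, and control/comparison (C), corresponding to ECT". For HAMD17 it assesses non-inferiority by "calculating the difference between the means of groups E and C and its 95% confidence interval at the end of the 12th session". The decision rule for that difference is given in the clause "which will then be compared to the NI margin (Ha: C-E < NI". The sentence gives a time point and two groups. It mentions no baseline, change or reduction.

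Section 2.10 sets the margin: the ECT-placebo difference "was 9.7 points (95% CI 5.7 to 13.5), with an NI value of 5.7".

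The direction of the scale follows from section 2.5: "Remission will be defined as a final HAMD17 score less than or equal to 7 points". Low scores are good and high scores are bad.

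Two other statements bear on the direction:

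- For AMT, section 2.9 uses the same order of subtraction: "controlled for age, years of schooling, and treatment-resistant depression (Ha: C-E < 0". As a statement that MST is superior, this fits a variable where larger is better.
- The Discussion describes the depression outcome on an improvement scale: "The primary outcome measure will be the reduction in depressive symptoms, assessed using the HAMD scale".

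Section 2.9 makes HAMD17 non-inferiority one of two conditions that must both hold for a positive result. The other is superiority on AMT.

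**The concern.** The order of subtraction and the side of the margin have to match the direction of the variable. If the means are HAMD17 scores, a worse MST has the higher mean, so C-E is negative. The condition C-E < 5.7 is then met more easily the worse MST is, and an MST that is clearly better than ECT is the one at risk of failing. If the means are reductions from baseline, C-E is the improvement given up by using MST, and C-E < 5.7 is the right alternative.

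Section 2.9 does not say which variable is meant, and its plain wording (group means of HAMD17 at a time point) points to the score. The direction of a co-primary decision rule therefore depends on something the analysis section leaves unsaid. An analysis program that copied the inequality and applied it to scores would give no protection against loss of antidepressant efficacy. The AMT condition does not measure that loss.

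**Working it through.** **Inputs.** Section 2.10 gives "α = 0.025 (one-tailed), β = 0.2, and a standard deviation of 9.5", a margin of 5.7 and 88 patients before attrition (100 enrolled, 50 per arm). Section 2.1 gives 1:1 allocation, hence 44 per arm. The true difference assumed in the sample size is not stated; I take it as 0. The protocol does not say whether the SD belongs to the score or to the change; I apply it to the analysed variable.

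**Step 1: reproduce the protocol's figure.**
n per arm = 2 × (1.960 + 0.842)² × 9.5² / 5.7² = 2 × 7.85 × 90.25 / 32.49 = 43.6, rounded up to 44, so 88 in total. This agrees with section 2.10. With a true difference of 0 the formula is symmetric in sign, so the sample size is the same whichever way the difference is taken.

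**Step 2: standard error.**
SE = 9.5 × √(2/44) = 2.025.

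**Step 3: probability of meeting the HAMD17 condition, applied to scores.** Let d be the true MST deficit (mean of E minus mean of C; positive means MST is worse).

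- Rule as written, upper 95% limit of C-E below 5.7: P = Φ((5.7 + d)/SE − 1.96).
- Rule oriented for a score, upper 95% limit of E-C below 5.7: P = Φ((5.7 − d)/SE − 1.96).

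| True d on HAMD17 score | As written | Oriented for a score |
|---|---|---|
| −5.7 (MST better) | 0.025 | 0.9999 |
| −2 (MST better) | 0.447 | 0.967 |
| 0 | 0.804 | 0.804 |
| 2 (MST worse) | 0.967 | 0.447 |
| 5.7 (MST worse, at the margin) | 0.9999 | 0.025 |
| 9.7 (the whole ECT-placebo difference) | about 1 | 0.00004 |

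Example at d = 5.7: (5.7 + 5.7)/2.025 − 1.96 = 3.67, and Φ(3.67) = 0.9999. With the other orientation, 0 − 1.96 gives 0.025.

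With 50 per arm, SE = 9.5 × √(2/50) = 1.90. The values at d = 5.7 are then above 0.9999 and 0.025.

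**Step 4: the same rule on reductions.** Reduction is baseline minus session-12 score. Randomised groups have equal expected baselines, so C-E on reductions has the same expectation as E-C on scores. The inequality C-E < 5.7 then behaves as in the right-hand column.

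**The case against.** The best defence is that the variable is reduction from baseline and the inequality is correct. Three things support this. The Discussion calls the outcome a reduction in symptoms. Section 2.10 gives the ECT-placebo difference as a positive 9.7, which is natural for a benefit. The AMT hypothesis in the same section also treats larger as better, so one C-E convention would cover both co-primary outcomes. In addition, section 2.9 calls the test non-inferiority and compares a confidence interval with the margin, so a statistician would probably notice a test that rewarded a worse MST.

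Much of this stands. It makes a notation slip or an unstated change of variable far more likely than an intended reversal. It does not settle the matter:

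- The operative sentence in section 2.9 gives means at a time point and says nothing about change, although section 2.7 speaks of changes in depression scores where change is meant.
- Section 2.10 describes the source of the margin as a difference in HAMD17 scores, and its positive sign may only be an absolute value.
- The Discussion paragraph names a single primary outcome and puts cognitive functioning among the secondary ones. That conflicts with the co-primary design in sections 2.5 and 2.9, so it is a weak basis for defining the analysed variable.

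It may also be said that a condensed article leaves such detail to a fuller document. That would answer an omission. Here a hypothesis is stated, and it is right or wrong depending on a variable the section does not name.

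**Conclusion.** The point holds as a defect in the written hypothesis: on the HAMD17 score, which is the plain reading of section 2.9, C-E < 5.7 is reversed; on reduction from baseline it is correct. The size, conditional on literal use with scores, is a probability of about 0.9999 instead of 0.025 of meeting the HAMD17 condition when MST is truly worse by the full margin. This rests on SD 9.5, 44 per arm and a normal approximation.

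A reader might infer that the trial is set to declare a much worse MST non-inferior, or that its overall type I error is near 100%. The documents support neither. Nothing shows that anyone intends the reversed rule, and several statements fit the correctly oriented one. The 0.9999 is for one of two required conditions and is not the probability of overall success, which also needs superiority on AMT. The sample size of 88 is unaffected.

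**What to change.** Name the analysed HAMD17 variable in section 2.9 and match the hypothesis to it. Either of these is sound:

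- **Score at session 12:** H0: mean(E) − mean(C) ≥ 5.7 against Ha: mean(E) − mean(C) < 5.7. Declare non-inferiority if the upper limit of the two-sided 95% confidence interval for MST minus ECT is below +5.7.
- **Reduction from baseline to session 12:** say so, and keep Ha: C-E < 5.7. Declare non-inferiority if the upper limit of the two-sided 95% confidence interval for ECT minus MST is below 5.7.

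Use the same variable in the Discussion and in any analysis plan or program. The cost is one sentence, with no change to sample size, visits or data collection. It should be settled before unblinding, so that the direction of a co-primary test cannot be disputed afterwards.

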**Figure 1 biomedicines-11-02150-f001:**
[figure not shown]
Study design (BL ECT, bilateral electroconvulsive therapy; MST, magnetic seizure therapy; HAMD17, Hamilton Depression Rating Scale, 17 items [17]).

Initially, patients will receive a total of 12 sessions, including the first successful titration session. If the first titration session fails to induce adequate seizures, it will not be considered as part of the total number of sessions. After the 12th session, a clinical assessment will be performed. If the patient meets the criteria for remission, defined as a score of 7 or less on the 17-item Hamilton Depression Scale (HAMD17) [17], the sessions will be discontinued, and the patient will undergo a neuropsychological evaluation. If the patient does not achieve remission, they will receive an additional 6 sessions, bringing the total to 18, and will be re-evaluated and undergo a neuropsychological assessment. In this case, regardless of the response or remission, treatment will be discontinued after the 18th session. This is because evidence suggests that the number of sessions required to achieve response and/or remission typically ranges from approximately 6 to 15 sessions [18].

Following the final session, participants will undergo a comprehensive evaluation, including medical assessment, neuropsychological evaluation, laboratory tests, and cranial MRI. Finally, patients will be followed up for 6 months after completing the intervention, with re-evaluations at 3 and 6 months.

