### 2.2. Ethical Considerations

The Local and National Ethics Committees approved the clinical trial study, which adheres to the Helsinki guidelines and their subsequent amendments. All recruited volunteers will undergo medical screening, during which the professional will explain the objectives, interventions, procedures, and potential risks of the trial. They will also receive a detailed consent form, and any questions will be answered. Written informed consent is required before starting the eligibility assessment, and patients can withdraw from participation at any time during the study. Patients who have an indication for ECT will be enrolled, as the risk of complications from ECT is low [16]. Patients will be closely monitored, and if their depression worsens, they will be discontinued from the study and treated accordingly. Participation may offer benefits such as psychiatric and psychological assessments, improvement in depression, standard care, and appropriate referrals. MRI safety criteria will be followed, and patients with contraindications will be excluded. The MRI is safe, and participants will not receive sedation, anesthesia, or contrast agents. Participants will receive medical feedback from a certified radiologist regarding their brain scan, which is a benefit.

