### 2.3. Eligibility Criteria

Trained psychiatrists/psychologists will review the diagnosis of depression using the Brazilian version of the Mini International Neuropsychiatric Interview 5.0.0 (MINI) [19], which was developed based on the *Diagnostic and Statistical Manual of Mental Disorders*, 4th edition (DSM-IV) and International Classification of Diseases and Related Health Problems, 10th revision (ICD-10). 

Inclusion criteria are: (a) age between 18 and 60 years; (b) diagnosis of major depressive disorder or depressive episode in bipolar disorder according to DSM-IV; (c) baseline HAMD17 score ≥17; (d) current TDR episode; (e) appropriate clinical condition for receiving ECT as assessed by a psychiatrist and an anesthesiologist; and (f) meeting transcranial magnetic stimulation (TMS) safety criteria [20]. In the definition of TRD for major depressive disorder, the utilization of a minimum of two prior treatment failures will be considered. Conversely, for TRD in bipolar depression, only one prior treatment failure will be required. In both cases, there must be confirmation of prior adequate dose and duration, based on clinical criteria evaluated using the Antidepressant Treatment History Form (ATHF) [21,22].

Exclusion criteria are: (a) pregnancy; (b) psychiatric comorbidity (except mild anxiety disorders); (c) depressive symptoms better explained by other clinical conditions or psychiatric disorders; (d) decompensated clinical and neurological conditions or serious sequelae of previous medical conditions; (e) use of psychoactive substances in the last 6 months (except nicotine); (f) use of monoamine oxidase inhibitors in the last 6 months; (g) application of ECT or another neuromodulation technique in the last 12 months; (h) contraindications for ECT or MRI; (i) relevant deviations in clinical laboratory parameters; or (j) inability to consent.

Discontinuation criteria are: (a) worsening depression; (b) development of suicidal ideation or suicide attempt; (c) withdraw consent; (d) development of (hypo)manic symptoms; (e) inability to induce seizures lasting at least 15 s after adjusting parameters and medications during the titration phase; (f) missing two consecutive treatment sessions; or (g) changes in drug treatment without the previous authorization.

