#### 2.4.3. MST

The MagVenture MagPro MST with Twincoil (Magventure, Farum, Denmark) will be used for MST sessions. The procedure will follow the same guidelines as ECT sessions regarding general anesthesia, oxygenation, motor activity monitoring, EEG, and postictal recovery. The Twin Coil will be centered over point Fz of the 10–20 system using an EEG cap to mark the correct point on the patient’s scalp.

The stimulation will be delivered with an amplitude of 100%, 100 Hz. In the first session, a titration of the convulsive threshold will be performed with a 2 s stimulus (200 pulses). If an adequate seizure is not triggered, the stimulus will be increased by two seconds (200 pulses) until a seizure is triggered or a maximum of 3 to 4 attempts is reached. If a seizure is not initiated in the first session, a new titration session will be scheduled. Medication will be reviewed and, if possible, the dose of benzodiazepines will be reduced depending on the opinion of the performing psychiatrist. The second titration session will repeat the same process as the first, with the parameters used in the last attempt. The maximum limit is set at 10 s of stimulation or until the coil temperature exceeds the safety limit. If no seizure is triggered in the second session, the patient will be excluded from the study. In subsequent sessions, the stimulus used will be 4 s (400 pulses) higher than the titration session, up to a maximum of 1000 pulses. If the patient has seizures of less than 20 s duration, the number of pulses will be increased by 200 pulses in the next session, until the seizures are effective or the limit of 1000 pulses is reached. These parameters were determined based on our previous experience [30].

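### The HAMD17 non-inferiority test has no all-randomised analysis: both sets are defined after randomisation, which can bias the result in either direction

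*Protocol article*

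**What the plan says.** All references are to the protocol article. Section 2.9 tests HAMD17 non-inferiority through the difference in group means and "its 95% confidence interval at the end of the 12th session, which will then be compared to the NI margin". The patients analysed are fixed in the next sentence: "Analyses will be performed on modified intent-to-treat (ITT) samples (at least 8 sessions of ECT/MST) and per-protocol (PP". For the other co-primary, AMT, the same section says: "Analyses will be performed on the ITT and PP sample". Trial success requires both results.

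The planned course is in Section 2.1, under Figure 1: "Initially, patients will receive a total of 12 sessions, including the first successful titration session". Remission is first checked after session 12.

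The ways to receive fewer sessions are in Section 2.3: "Discontinuation criteria are: (a) worsening depression; (b) development of suicidal ideation or suicide attempt; (c) withdraw consent; (d) development of (hypo)manic symptoms". That list continues with failed seizure induction in titration, two consecutive missed sessions and unauthorised drug changes. Section 2.2 says of patients that "if their depression worsens, they will be discontinued from the study and treated accordingly". Section 2.4.3 adds for MST: "If no seizure is triggered in the second session, the patient will be excluded from the study". Section 2.4.2 has the equivalent rule for ECT.

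**The concern.** A minimum of 8 of the 12 planned sessions selects patients on something that happens after allocation. Remission is not assessed before session 12, so the plan gives no route out before session 8 for a patient who is doing well. Several of the listed routes are failures of the allocated treatment: worsening, suicidality, and no seizure despite two titration sessions. These patients disappear from the HAMD17 comparison. The article does not define the per-protocol set, but such a set also depends on treatment received and would not normally bring them back.

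Non-inferiority testing is exposed to this because losing failures can make two arms look more alike. The margin leaves little room for it: Section 2.10 sets 5.7 points, the lower confidence limit of the ECT-versus-sham difference, and itself calls the margin large. A false claim at that boundary could mean that MST keeps little of the demonstrated ECT effect.

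**Working it through.** **Inputs.** From Sections 2.9 and 2.10: one-sided alpha 0.025, power 0.80, SD 9.5, margin 5.7, 88 patients needed, 100 enrolled (50 per arm). Early-exit rates and the scores of those who exit are not given. They are assumptions below.

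**The plan's own figure.** n per arm = 2 × [9.5 × (1.960 + 0.842) / 5.7]² = 43.6, so 44 per arm and 88 in total, as stated. Allowing 10% attrition, 88 / 0.9 = 97.8, consistent with 100. The sample size is not in question.

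**Standard error.** With 44 analysed per arm, SE = 9.5 × √(2/44) = 2.03 (2.025 before rounding).

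**Effect of the restriction.** Take the difference as MST minus ECT, higher being worse. Suppose a fraction qE of MST and qC of ECT patients leave before session 8, and in each arm they score d points worse than those retained. Then

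- all-randomised difference = retained difference + d × (qE − qC);
- with the all-randomised difference at the margin, P(declare non-inferiority) = Φ(d × (qE − qC) / 2.025 − 1.96).

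| Excess of early exits | d (points) | Shift | Retained difference | One-sided type I error |
|---|---|---|---|---|
| none | any, equal in both arms | 0 | 5.7 | 2.5% |
| MST, 4 percentage points | 10 | 0.4 | 5.3 | 3.9% |
| MST, 10 percentage points | 5 | 0.5 | 5.2 | 4.3% |
| MST, 8 percentage points | 10 | 0.8 | 4.9 | 5.9% |
| MST, 8 percentage points | 15 | 1.2 | 4.5 | 8.6% |
| MST, 10 percentage points | 15 | 1.5 | 4.2 | 11.1% |
| ECT, 8 percentage points | 10 | −0.8 | 6.5 | 0.9% |
| ECT, 8 percentage points | 15 | −1.2 | 6.9 | 0.5% |

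Example: 0.8 / 2.025 = 0.395, and Φ(0.395 − 1.96) = Φ(−1.565) = 5.9%.

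**A second model without arm-specific rates.** Apply one exit rule to both arms, driven by early clinical status, with 50 randomised per arm and MST truly 5.7 points worse. MST then loses more patients simply because it works less well. If early status correlates 0.5 to 0.7 with the endpoint and 5 to 10% of ECT patients leave, type I error is 3.7% to 7.6%. In the extreme case where the rule removes the worst endpoint scores directly, with 5% of ECT and hence 14.8% of MST patients removed, the retained difference is 4.15 and type I error is 14.6%.

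**The case against.** The strongest reply is that direction and size are not in the documents. No exit rates by arm are given. The bias is zero when rates and penalties are equal, and it reverses if ECT loses more patients, which the cognitive burden of bitemporal ECT makes plausible. A gap of 10 to 15 points exceeds the planning SD of 9.5. All of this stands, so the figures are scenarios and not estimates.

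Three stronger readings are tempting but unsupported:

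- *MST must fail titration more often because it has a pulse cap and a coil-temperature limit.* Section 2.4.2 gives ECT a ceiling too, the device's maximum load. Both arms share the limit of 3 to 4 attempts and the exclusion after a second failed titration session.
- *The two co-primaries are analysed on two different populations.* The abbreviation ITT is introduced in Section 2.9 next to the 8-session definition, so the AMT paragraph may mean that same set. The text is ambiguous; it does not establish two populations.
- *Everyone removed is a treatment failure.* Missed sessions need not reflect efficacy, and a patient with a (hypo)manic switch may have a low HAMD17. (Hypo)manic events are also compared between arms separately.

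It can also be said that an all-randomised analysis is not free of bias. Patients who worsen receive other treatment, and if MST failures improve on it, their later scores also pull towards non-inferiority. That is correct, and the remedy has to address it. None of these replies supplies an all-randomised HAMD17 analysis. An analysis plan that is not shown does not cure sets that the article fixes explicitly.

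**Conclusion.** The point holds in this form: the HAMD17 non-inferiority conclusion rests only on sets defined by what happens after randomisation, and its type I error is not controlled where control matters most, when MST is worse and loses more early failures. A reader might infer that the rule is certain to favour MST; the documents do not show that.

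Under the stated assumptions (true deficit 5.7, 44 per arm, SD 9.5, normal approximation), 8 percentage points more early exits under MST with a penalty of 10 to 15 points gives 5.9–8.6% instead of 2.5%. Equal rates and penalties give 2.5%, and the same excess under ECT gives 0.5–0.9%. Whether ITT for AMT means all randomised patients or those with 8 sessions also needs to be stated. Because this concerns the validity of a co-primary conclusion, it should be settled before analysis. It should also be settled early, since outcomes not collected after discontinuation cannot be recovered.

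**What to change.** 1. Make the primary HAMD17 analysis all randomised patients as allocated, in a mixed model on the scores at baseline, after session 6 and after session 12. The test against 5.7 uses the session-12 contrast.
2. Continue the planned HAMD17 and AMT assessments after study treatment stops, where the patient agrees. Without this, a patient who fails titration contributes only a baseline score. The same holds for AMT in anyone who leaves early, as Table 2 has no AMT between baseline and the post-acute visit.
3. State in advance how scores obtained after other treatment starts enter the primary analysis.
4. Add a sensitivity analysis giving early failures an unfavourable session-12 value.
5. Use the same all-randomised set for both co-primaries and define ITT once.
6. Keep the 8-session and per-protocol sets as supportive.

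The cost is wording in the protocol and analysis plan, a few extra outcome visits, a somewhat larger SD, and some scores affected by later treatment. No treatment or discontinuation rule has to change.
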